### Trial design {8}

This study is a parallel-group randomized controlled comparative effectiveness trial with five arms:1) the Combined Shamiri Intervention (consisting of a growth element, a gratitude element, and a value affirmation element; henceforth called “Shamiri”), 2) the Growth Intervention, which encompasses content related to growth mindset and strategies for growth, 3) the Gratitude Intervention, which incorporates content to build feelings of gratitude and expression of gratitude, 4) the value affirmation intervention, which incorporates content to help students identify and better act on their personal values and sense of purpose, and 5) a study skills control group, an active control group teaching students study skills that may be useful to them as students. Each condition is described further below under “interventions.” Participants will be allocated within each school to the five conditions with a 1:1:1:1:1 ratio, or equal probability for assignment to each condition. Each arm will require 4-h-long sessions spanning 4 weeks and will be delivered in a group (8–15 students) setting by a local, trained lay provider between the ages of 18 and 24. Measures of mental health, wellbeing, and character strengths will be collected at baseline, 2-week midpoint, 4-week endpoint, and 1-month, 3-month, 6-month, and 9-month follow-up. Academic data will be collected for the school terms before, during, and after the intervention. De-identified trial data will be available in an online repository and upon request.

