### Sample size {14}

We conducted a power analysis using Optimal Design, a statistical simulation software which can estimate sample size for randomized controlled trials assessed using multi-level (i.e., mixed effects) models [74]. In Optimal Design, we estimated the required sample size for a person-randomized trial with six-time repeated measures (baseline, midpoint, post, 1-month follow-up, 3-month follow-up, 6-month follow-up, and 9-month follow-up). Additionally, for each outcome measure, we have four contrasts of primary interest (each intervention condition compared to the control), thus, using a conservative *p* value correction, we would divide the typical alpha value of .05 by four and get a *p* value threshold for significance of .0125. Finally, we assumed that we are interested in detecting a minimum post-treatment effect size of .3. We selected this value for the following reasons: 1) it is slightly lower than the effect sizes found in most previous trials of Shamiri, which range from .32–.83 at the latest follow-up points [3, 20, 33, 34], which will allow us to detect potentially smaller effects of the individual component interventions, and to detect effects in a universal sample, and 2) a standardized effects size of .3, which is considered small to medium, remains clinically meaningful and important in our view, whereas a change smaller than that may not be as clinically meaningful. Given these parameters, we found that a sample of 515 students would be needed to conduct a two-group trial with a power of .80. So, for this five-group trial, we multiplied that by 2.5, to get a final target sample size of 1288 students. Because in a past trial with 7-month follow-up there was a high dropout rate during follow-up of up to 40% [33], we will initially invite 2147 students to the sessions, assuming that around 40% of them will drop out prior to the sessions or during the follow-up period.

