## Assignment of interventions: allocation

### Sequence generation {16a}

After the baseline assessment, youths who opt to participate in the study will be randomly allocated within each school to one of the four intervention conditions or to the study skills control condition (with equal probability for assignment to each condition) using a computerized random number generator in R. Randomization will be stratified by reported age and gender in the case of mixed-gender schools, as well as by level of symptoms at baseline (i.e., GAD-7 and PHQ-8 scores).

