## Statistical methods

### Statistical methods for primary and secondary outcomes {20a}

Outcome measures will only be analyzed if they demonstrate internal consistency within the full sample at baseline, defined as an alpha value of .70 or above [75]. For those outcome measures that pass this threshold, all main analyses of primary and secondary outcomes will follow an intent-to-treat approach, meaning that all participants who consent, are randomized into the groups, and complete baseline measures will be included in all analyses (see 20c below for more about plans for handling missing data).

For all analyses of primary and secondary outcomes, we plan to use linear mixed effects models to model time × condition interaction with a random intercept for participant ID to allow for individual variation at baseline. We plan to control for age and sex in all models of primary and secondary outcomes. Age will be included because older adolescents report increased psychosocial stress and thus greater risk of mental illness [3]. Similarly, sex differences in anxiety and depression are widely documented in adolescents including Kenyan adolescents [3, 76]. Additionally, the authors will test more complicated random effects structures which reflect the hierarchical structure of the data, including random effects for groups within group leaders, crossed random effects for schools and group leaders, and for participants in groups. We will also test adding a random slope for participant ID and for school; however, these added random effects may result in overfitting, which would reduce the generalizability of our findings. If this is the case, we will select a more parsimonious model with a simpler random effects structure. These variables (group leader, school, and group) will also be tested as covariates rather than random effects in the model, and final model selection will be done taking into account both overfitting warnings and Akaike Information Criterion (AIC) [77].

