Primary models will include all five groups, using the control group as the contrast group. Secondary models will include the four intervention conditions, using the full Shamiri intervention as the contrast group. Significant (*p* < .05 with a Holm-Bonferroni correction to account for four comparisons within each model) time × condition interactions will indicate that one condition produced significantly steeper improvements than another condition across the time included in the analyses. As described above and per recommendations outlined in past literature [78], the Holm-Bonferroni correction will be applied at a family-wise level (i.e., to account for multiple group comparisons on each outcome), rather than at a study-wise level.

Additionally, for all pairwise contrasts (including those comparing active interventions to each other) on all primary and secondary outcomes, effect sizes will be calculated as mean gain scores, to compare change within the various intervention and control groups.

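### Allocation is within school and stratified on baseline PHQ-8 and GAD-7, but the models commit only to age and sex and appear to leave baseline means free by arm, so some available precision is lost

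*Protocol article*

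**What the plan says.** **Allocation.** Trial design {8}: "Participants will be allocated within each school to the five conditions with a 1:1:1:1:1 ratio". Sequence generation {16a} repeats that students "will be randomly allocated within each school to one of the four intervention conditions or to the study skills control condition". It stratifies by age, by gender in mixed-gender schools, "as well as by level of symptoms at baseline (i.e., GAD-7 and PHQ-8 scores").

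**Model.** Section {20a} plans "linear mixed effects models to model time × condition interaction with a random intercept for participant ID to allow for individual variation at baseline". The covariates promised for every model are these: "We plan to control for age and sex in all models of primary and secondary outcomes". School, group leader and group are tried as random effects, and then: "These variables (group leader, school, and group) will also be tested as covariates rather than random effects in the model". AIC and overfitting warnings decide what is kept. Baseline PHQ-8 and GAD-7 are not named as covariates anywhere. Section {20b} adds that the main analyses will include no additional adjusted analyses.

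**Role of baseline.** Sample size {14} counts baseline among the repeated measures: "six-time repeated measures (baseline, midpoint, post, 1-month follow-up, 3-month follow-up, 6-month follow-up, and 9-month follow-up"). Seven occasions are listed, although the text says six. The test is whether one condition improves more steeply than another, and for pairwise contrasts "effect sizes will be calculated as mean gain scores".

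**Timing.** Participant timeline {13} puts the baseline of the primary questionnaires and some secondary outcomes before allocation. The remaining secondary baselines are taken after allocation, just before the first session.

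**The concern.** Three of the factors that shaped the allocation (school, PHQ-8, GAD-7) are either left to a data-driven choice or left out. More important for precision is how the outcome's own baseline is used. If each arm has its own baseline mean, the time × condition term compares change from baseline. Randomisation makes the arm means equal in expectation for any baseline measured before allocation, and an analysis that uses this has smaller variance at no cost. At stake are the width of the intervals and the power of each primary contrast, in a trial that expects up to 40% dropout and wants to detect possibly smaller effects of single components.

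**Working it through.** **1. The plan's own figure.** Inputs from {14}: d = .3, alpha .05/4 = .0125 (taken as two-sided), power .80, 515 students for two groups.

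- A plain two-mean comparison with 257.5 per arm gives power .818, close to .80. Solving for n gives 248 per arm, 496 in total.
- The repeated-measures form gives 517 (seven occasions, residual-to-slope variance ratio 1) or 513 (six occasions, ratio 0.5). The ratio is an assumption, because the text gives none.
- 515 × 2.5 = 1287.5, so 1288. 1288/0.6 = 2146.7, so 2147.

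The sample size is reproduced without any credit for baseline adjustment.

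**2. Assumptions for the comparison.** Outcome variance 1 at each visit; equal correlation ρ between any two visits (random intercept only); complete data; no clustering. ρ is not in the documents, so .3 to .8 is shown.

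**3. Single-visit contrast.** The variance is proportional to 2(1−ρ) for a change score and to 1−ρ² with baseline adjustment or a common baseline mean. The ratio is (1+ρ)/2. Power is Φ[.3/(s√(2/n)) − 2.498] with n = 1288/5 = 257.6 and s² the variance in the table.

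| ρ | change | adjusted | ratio | power, change | power, adjusted | n per arm for 80% |
|---|---|---|---|---|---|---|
| .3 | 1.40 | .91 | .65 | .648 | .858 | 347 v 226 |
| .5 | 1.00 | .75 | .75 | .818 | .924 | 248 v 186 |
| .7 | .60 | .51 | .85 | .971 | .988 | 149 v 127 |
| .8 | .40 | .36 | .90 | .998 | .999 | 100 v 90 |

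At ρ = .5: .3/√(2/257.6) = 3.405. Then 3.405 − 2.498 = .907 gives .818, and 3.405/.866 − 2.498 = 1.434 gives .924.

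**4. Linear time × condition term.** For m visits at times t, the variance ratio (common to free baseline mean) is

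[Σt² − (Σt)²/m] / [Σt² − ρ(Σt)²/(1+(m−1)ρ)].

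- Seven visits, weeks 0, 2, 4, 8, 17, 30, 43 (follow-ups counted from the 4-week endpoint): Σt = 104, Σt² = 3122. At ρ = .5: (3122 − 1545.1)/(3122 − 1352) = 1576.9/1770 = .891.
- Baseline to 1 month, weeks 0, 2, 4, 8: Σt = 14, Σt² = 84. At ρ = .5: 35/(84 − 39.2) = .781.
- Three grade terms, equally spaced: Σt = 3, Σt² = 5. At ρ = .5: 2/(5 − 2.25) = .727.

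| Contrast | ρ = .3 | ρ = .5 | ρ = .8 |
|---|---|---|---|
| Seven-visit slope | .803 | .891 | .967 |
| Baseline to 1 month | .660 | .781 | .924 |
| Three grade terms | .604 | .727 | .897 |

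A random slope shrinks these gains somewhat. With an assumed slope variance of .2 (at the last visit), the seven-visit ratio at ρ = .5 is .919 and the baseline-to-1-month ratio .821.

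**5. What the missing covariates do by themselves.** With complete data and a participant random intercept, time × condition is a within-person contrast, so a covariate that is constant over time cancels. A small simulation (four visits, assumed variances) agrees: the standard error was 0.01185 with no covariates, with school, and with school plus a baseline covariate. A common baseline mean reduced it to 0.01070.

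**6. A trap in the remedy.** If the arms share a baseline mean and the same baseline is also entered as a covariate, the standard error is understated. In null simulations at assumed correlation .5 (n = 200, 700 runs) the mean SE was .0096 against a true SD of .0104, with 7.3% rejections at nominal 5%; the constraint alone gave 4.0%. A second simulation gave .0095 against .0112, and 8.4%.

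**The case against.** The strongest reply has four parts.

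- **The article is condensed and does not say that baseline means are free.** True: this is read from the interaction model and the gain scores. But the article does state its covariates with reasons, and {20b} plans no further adjusted main analyses, so the covariate set is not simply left open.
- **The plan is not blind to the design.** True. Age and gender are themselves stratification factors and are adjusted for, school is a listed candidate as random effect or covariate, and each outcome's baseline is in the model as a response. Precision is therefore lost in part, not thrown away. The fault on school is that its inclusion is conditional.
- **The planned test is a trajectory, so single-visit gains are not the relevant size.** Largely fair. For the seven-visit slope the gain is only 11% at ρ = .5. But {21b} expects the visits up to 1 month to be reported first, where it is 22%, and the single-visit case matches the gain-score effect sizes.
- **Not every baseline precedes allocation.** True, and section {18b} implies that students who miss the first session may be removed, which could weaken the equal-baseline premise. The fix has to be limited accordingly.

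A reader might also infer that omitting the strata by itself makes the time × condition standard errors too large. Step 5 shows that it does not: school and symptom main effects change nothing there while baseline means stay free. A larger saving could be computed for an average over all follow-ups, but the plan tests no such average.

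**Conclusion.** The point holds as one of efficiency. The design uses school, PHQ-8 and GAD-7, and the analysis as described does not commit to using them, nor to using the equality of arms at baseline. Under the assumptions in step 2, with ρ from .3 to .8, the available variance reduction is:

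- about 3–20% for the seven-visit slope (11% at .5);
- 8–34% for baseline to 1 month (22%);
- 10–40% for three equally spaced grade terms (27%);
- 10–35% for a single visit (25%, power .82 to .92).

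At the upper end of the range the power gain is negligible. All of this rests on the inference that baseline means are free by arm.

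A reader might go further and conclude that the planned analysis is biased, has inflated type I error, or that 1288 is wrong. The documents support none of these. The target takes no credit for baseline adjustment, so the change would add power at the same N.

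**What to change.** Amend {20a}:

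1. For outcomes whose baseline precedes allocation, choose one of two forms in advance. Either constrain the arms to a common baseline mean (time coded zero at baseline, no condition main effect), or model follow-up visits only with the outcome's own baseline as a covariate. Never use the same baseline as both response and covariate in one model. Pre-intervention grades qualify: they refer to the January–April term, even though they are collected later.
2. Prespecify school as a fixed effect in all models instead of leaving it to AIC. With 5–12 schools a random-effect variance would be poorly estimated, and this also removes one outcome-dependent choice.
3. Add baseline PHQ-8 and GAD-7 as covariates beside age and sex wherever they are not already the response at baseline. With a common baseline mean, the PHQ-8 model would take GAD-7 only, and the reverse.
4. For secondary outcomes whose baseline is taken after allocation, do not impose the common mean. Adjust for school and the pre-allocation PHQ-8 and GAD-7, with age and sex.
5. Report baseline-adjusted differences beside the mean gain scores.

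The cost is wording and model code. School, PHQ-8 and GAD-7 are known before allocation, so no further data or participants are needed.

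### Model-fit criteria decide whether delivery-group clustering is modelled, and no named candidate covers group differences in change, so the time × condition standard error will be too small if groups differ in change

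*Protocol article*

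**What the plan says.** All references are to the Protocol article.

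- **Design.** Trial design {8} allocates students individually within school to five arms and delivers every arm in groups of 8–15 led by a lay provider. Under Implementation {16c}, groups are filled after allocation according to the assigned condition, so each group belongs to one arm.
- **Committed model.** In Statistical methods {20a}, "we plan to use linear mixed effects models to model time × condition interaction with a random intercept for participant ID". Age and sex are added as covariates.
- **Optional terms.** Random effects for groups within leaders, for schools crossed with leaders, and for participants in groups will be tried. Slopes are named separately: "We will also test adding a random slope for participant ID and for school; however, these added random effects may result in overfitting". The fallback is: "If this is the case, we will select a more parsimonious model with a simpler random effects structure". There is also a fixed-effect alternative: "These variables (group leader, school, and group) will also be tested as covariates rather than random effects in the model". Overfitting warnings and AIC settle the choice.
- **Test.** The same section reads a significant time × condition interaction, Holm-corrected over four comparisons, as the evidence that one condition improves more steeply than another.
- **Sample size {14}.** The calculation is for a person-randomized trial and states no ICC or design effect: "a sample of 515 students would be needed to conduct a two-group trial with a power of .80".

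**The concern.** Students in one group share a leader, sessions and discussion, so their changes over time may be correlated. Groups sit inside arms, so that correlation adds to the variance of every between-arm comparison of change. Three features of the stated rule leave it unaccounted for.

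1. Delivery group is a feature of the design, yet model fit decides whether it is modelled.
2. The terms named for group are not slopes. A group effect that is constant over time, random or fixed, drops out of within-person change and leaves the interaction's standard error essentially as it was. A school slope does not help because all five arms run in each school. A participant slope treats students in the same group as independent.
3. Selection can be made separately by outcome, so the primary outcomes could end up with different error structures.

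Every comparison with control, and every single-component comparison with full Shamiri, rests on this standard error. If it is too small, false claims that a component works become more frequent than the Holm procedure is meant to allow.

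**Working it through.** **1. The plan's own sample size.** Inputs from Sample size {14}: "we would divide the typical alpha value of .05 by four", giving .0125; "interested in detecting a minimum post-treatment effect size of .3"; power .80. Two-sided testing is assumed. Per arm, n = 2(z₀.₉₉₃₇₅ + z₀.₈₀)²/d² = 2(2.498 + 0.842)²/0.09 = 247.8, so 248 per arm and 496 in total (500 with the noncentral t). The stated 515 is within about 4% of this. The software's variance inputs are not reported, so an exact match is not possible. Then 515 × 2.5 = 1287.5, rounded to 1288, and 1288/0.6 = 2147 invited. The figure is close to a plain two-sample calculation, with no visible allowance for delivery groups.

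**2. Number of groups.** 1288/5 ≈ 258 per arm, which gives 17 groups of 15 to 32 groups of 8. The figures below use 12 per group, about 21 groups per arm.

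**3. Formula.** When group variation in slopes is omitted but a participant slope is present, the design effect is DE = 1 + (m − 1) × ICC. The ICC here is that of the *observed* person slopes. The reported standard error is 1/√DE of the true one, and actual α = 2[1 − Φ(z/√DE)].

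**4. ICC read as that of observed slopes (assumed values, m = 12).**

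| ICC | DE | SE ratio | actual α at .05 | at .0125 |
|---|---|---|---|---|
| .02 | 1.22 | 0.91 | .076 | .024 |
| .05 | 1.55 | 0.80 | .115 | .045 |
| .10 | 2.10 | 0.69 | .176 | .085 |

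Two separate simulations (3000 runs; seven assessments at 0, 0.5, 1, 2, 4, 7 and 10 months; complete data) gave .071/.122/.180 and .088/.112/.176 at nominal .05. A group-level analysis in the same simulations stayed at .046–.058.

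**5. ICC read as that of true slopes.** Assume within-person correlation .5 and person-slope SD .03 per month. The seven times have Σ(t − t̄)² = 84.5, so slope error variance is .5/84.5 = .0059, against true slope variance .03² = .0009. An ICC of .02/.05/.10 on true slopes is then an observed-slope ICC of ICC × .0009/.0068 = .0026/.0066/.0132.

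| true-slope ICC | DE | actual α at .05 | at .0125 |
|---|---|---|---|
| .02 | 1.03 | .053 | .014 |
| .05 | 1.07 | .058 | .016 |
| .10 | 1.15 | .067 | .020 |

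Conversely, the step 4 values of .02/.05/.10 would need groups to account for about 13%/29%/46% of all true slope variance. The result also depends on the slope SD. If half of the observed slope variance is real, simulated α at nominal .0125 for true-slope ICC .02/.05/.10 is .014–.023/.021–.028/.035–.055, over groups of 8 to 15.

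**6. AIC as gatekeeper.** In that last simulation a group slope was offered as a candidate and AIC judged it. AIC discarded a real group slope variance in about 83–85% of trials at ICC .02, 40–55% at .05 and 5–11% at .10. With the group slope always kept, α was .011–.015.

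**7. Power with a correct standard error.** For 515 in two groups, power = Φ(0.3√(515/(4·DE)) − 2.498). This gives .82 with no clustering, .80/.78/.75 for the step 5 design effects and .72/.59/.44 for those of step 4.

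**The case against.** - **The list of random effects is open-ended.** It is introduced as a set of examples and does not say that the group terms are intercepts, so a group slope is not excluded. That stands. But slopes are named separately for participant and school only, nothing commits to one for group, and any added term remains removable.
- **Such detail belongs in a statistical analysis plan.** This would answer a complaint about missing detail. The complaint here is about a selection rule that the protocol states.
- **The size is unknown.** This stands. No ICC is given, and the choice of scale alone moves the result from slight to serious. The simulations also assume seven complete assessments. Academic performance has only three terms, and dropout of up to 40% would shrink the observed groups.
- **The participant-intercept model is not the expected outcome.** A reader might take that model's error rates as the headline: .092/.151/.228 at nominal .05 for observed-slope ICC .02/.05/.10. The documents do not support this. A participant slope is a listed candidate, and under the same assumptions AIC kept it in 93% of simulated trials with no group effect and in 99–100% with one. Those rates also mix two faults, and they vary with the assumed slope variance. The plan permits the intercept-only model, and inflation would then be larger, but AIC would usually not choose it.
- **Group as a fixed covariate.** A reader might infer that the test is invalid because group is aliased with condition. The aliasing affects the condition main effect. The tested interaction stays estimable. The valid criticism is that the covariate leaves the interaction's standard error uncorrected.

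**Conclusion.** The point holds in conditional form. The protocol lets AIC and overfitting warnings decide whether delivery-group clustering is modelled, and no candidate it names covers group differences in change. The time × condition standard error will be too small if such differences exist. A reader might infer that it is too small outright, but the documents contain nothing that shows groups differ in change, or by how much.

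With 12 per group and a participant slope in the model, type I error at nominal .05 is about .07–.18 for an observed-slope ICC of .02–.10, and about .053–.067 for a true-slope ICC of .02–.10 with slope SD .03 per month. Both ranges rest on assumed ICCs, balanced complete data and seven assessments. The direction is firm and the magnitude is not. It merits correction before analysis because all the confirmatory comparisons use this standard error and the remedy needs no new data.

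**What to change.** Replace the selection rule in Statistical methods {20a} with a fixed structure for every primary outcome:

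- a participant random intercept and slope, plus a delivery-group random effect on change in the same form as the tested time term (a group slope if time is linear, a post-baseline group effect if the test is of a post-baseline difference);
- these terms retained regardless of AIC, with small-sample degrees of freedom (Kenward-Roger or Satterthwaite);
- group as a fixed covariate removed as an alternative way of handling clustering;
- if the model does not converge, small-sample cluster-robust standard errors by delivery group, not a return to the participant-intercept model.

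This is a change of wording. The only extra variable is group membership, which the study team assigns. The price is wider confidence intervals and power below the stated .80 if the group ICC is not negligible: for the two-group 515, about .75 at a true-slope ICC of .10 and about .59 at an observed-slope ICC of .05, under the assumptions above. The sample size section should state the ICC assumed and the power that results.

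### The Holm-Bonferroni count of four does not fit the secondary models against full Shamiri, which hold three contrasts; the error is conservative and small

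*Protocol article*

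**What the plan says.** The section Statistical methods for primary and secondary outcomes {20a} describes two kinds of model. The first: "Primary models will include all five groups, using the control group as the contrast group". The second: "Secondary models will include the four intervention conditions, using the full Shamiri intervention as the contrast group". One rule for significance then covers both, p < .05 "with a Holm-Bonferroni correction to account for four comparisons within each model". The section goes on to define the family: "the Holm-Bonferroni correction will be applied at a family-wise level (i.e., to account for multiple group comparisons on each outcome"), as opposed to across the whole study.

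The origin of the four is in Sample size {14}, which speaks of "four contrasts of primary interest (each intervention condition compared to the control") and continues: "we would divide the typical alpha value of .05 by four and get a *p* value threshold for significance of .0125". The abstract describes the second set of comparisons as the single-element interventions against full Shamiri. The article gives no separate count for the secondary models.

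**The concern.** A model with k arms and one reference arm has k − 1 contrasts with that reference. The count of four comes from the comparisons with control and appears to have been carried over to a model with one arm fewer. An analyst who follows the text would apply thresholds built for four tests to three p-values, and each Holm step would then be stricter than the 5% family-wise level requires.

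The tests affected are those of growth, gratitude and values against the combined intervention. The Background names the missing comparison between single elements and the three-component package as a limitation of the earlier microtrial, so these tests matter to the trial although they are not its primary contrasts. What is at stake is some power, together with a decision threshold that the text leaves open to more than one reading.

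**Working it through.** **Inputs**
- Family-wise alpha .05 and divisor 4: Sample size {14}. Sidedness is not stated; two-sided tests are assumed.
- Primary models: five arms, control as reference ({20a}).
- Secondary models: four arms, full Shamiri as reference ({20a}).
- Total target 1288 with equal allocation (Sample size {14}; Trial design {8}), so 1288 / 5 = 257.6 per arm.
- Planning effect: "we are interested in detecting a minimum post-treatment effect size of .3". It is set for the comparisons with control; using it for component versus Shamiri is an assumption.

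**The plan's own figures.** .05 / 4 = .0125, as stated. The article reports that "a sample of 515 students would be needed to conduct a two-group trial with a power of .80", and 515 × 2.5 = 1287.5, rounded to 1288. A simple two-mean formula at d = .3, two-sided alpha .0125 and power .80 gives 2 × ((2.498 + .842) / .3)² ≈ 248 per arm, or 496 in total. That is near 515, which came from a repeated-measures program whose other inputs are not given.

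**Count of contrasts.** Primary models: 5 − 1 = 4. Secondary models: 4 − 1 = 3. This takes one time × condition term per non-reference arm, which fits the section's reading of the interaction as a difference in steepness of improvement.

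**Holm steps for the three Shamiri contrasts**

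| Ordered p-value | Count of 4, as written | Count of 3 |
|---|---|---|
| smallest | .05/4 = .0125 | .05/3 = .0167 |
| second | .05/3 = .0167 | .05/2 = .025 |
| largest | .05/2 = .025 | .05/1 = .05 |

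If the smallest p-value lies between .0125 and .0167, the procedure stops at once under a count of four and rejects nothing. Under a count of three it rejects that contrast and goes on.

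**Cost at the first step.** Assume a contrast has power .80 at .0125. Its noncentrality is 2.498 + .842 = 3.339 (from unrounded values). The critical value at .0167 is 2.394, so power is Φ(3.339 − 2.394) = Φ(.945) = .828. Alternatively, with d = .3 and 257.6 per arm, the noncentrality is .3 × √(257.6/2) = 3.405. Power is then Φ(3.405 − 2.498) = .818 at .0125 and Φ(3.405 − 2.394) = .844 at .0167, a difference of 2.6 points.

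**Cost over all steps.** This was simulated with three contrasts sharing one reference arm, 257.6 per arm, no clustering and 400,000 replicates:

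| Assumed true differences | Quantity | Count of 4 | Count of 3 |
|---|---|---|---|
| none | family-wise error | .034 | .045 |
| all three .3 | power per contrast | .86 | .90 |
| all three .3 | all three rejected | .74 | .82 |
| all three .2 | power per contrast | .45 | .52 |

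**The other reading of the family.** If both models on one outcome formed a single family, it would hold 4 + 3 = 7 contrasts and the first threshold would be .05 / 7 = .0071. Four is then too few.

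**The case against.** The strongest reply is that the slip is harmless. It errs on the safe side and leaves untouched the comparisons with control, which fix the sample size and carry the only stated hypothesis. It falls on what the article itself calls secondary models. At the first step the loss is under three points of power; the larger losses arise when all three differences are real, at effect sizes the protocol does not give for these contrasts. All of this stands and limits the weight of the point. It does not make the count right.

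A second reply is that over-correction is not certain, because defining the family by outcome could pool both models. That also stands in part. The explicit per-model wording favours three, but on neither reading is four the right number for the Shamiri contrasts, so the family has to be stated.

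A reader might go further in three ways that the document does not support:
- That these contrasts are expected to be smaller than those with control and so suffer most. The article gives no expected effect for a single element against Shamiri.
- That the secondary models are faulty because they leave out the control arm and should be replaced by contrasts from the five-arm fit. A fit to the four active arms is a valid analysis of the same randomised contrasts. About 4 × 257.6 ≈ 1030 participants remain to estimate variances and covariate effects, and no material loss has been shown.
- That the correction would help show that a component matches the package. That is a question of equivalence, which a less strict threshold for detecting a difference cannot answer.

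**Conclusion.** The count is wrong for the secondary models. Under the stated per-model family, the three component-versus-Shamiri tests should use Holm steps of .0167, .025 and .05, and the text as written gives .0125, .0167 and .025. The article fixes this number itself, so it is a misstatement and not detail left to an analysis plan.

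The consequence is modest. Family-wise error under the global null falls to about .034, below the permitted .05, and the primary comparisons keep their correct count of four. The loss is about 3 points of power at the first step. It is about 4 to 7 points per contrast if all three differences are real and equal to .3 or .2. These power figures assume two-sided tests, a two-mean approximation without clustering, and effect sizes the protocol does not state for these contrasts, so they indicate scale only. The count of contrasts depends on none of them.

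**What to change.** Replace the single count with a sentence such as: Holm-Bonferroni will be applied over four comparisons in each primary model and over three in each secondary model, the family being the set of contrasts within one model for one outcome. The last clause matters because it rules out the pooled reading with seven contrasts and leaves no choice among .0071, .0125 and .0167 once data are seen.

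The cost is one sentence. Sample size, data collection and the primary analysis do not change, and family-wise error within each model and outcome stays at or below 5%. If the investigators do intend one family of seven per outcome, they should say so. The threshold for the comparisons with control, and the .0125 behind the sample size, would then need revisiting.
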